### Data analysis plan

The primary outcome will be analysed using a repeated-measure linear mixed model including all available SOFAS scores measured at months 0, 3, 6, 12, and 24. Fixed effects will include the randomised group, visit as a categorical variable, and the interaction between group and visit. The baseline SOFAS score will be included as a covariate alongside sex, age, and site (stratification variables). To account for correlations between repeated measures, a random patient intercept will be included. In case of convergence issues with the inclusion of the random effect, we will replace the random effect with a repeated effect assuming a compound symmetry covariance structure. This model will be used to derive the effect of the intervention at 12 months, expressed as the adjusted mean difference and its 95% confidence interval. The effect of the intervention at other timepoints will be estimated using a similar approach.

Secondary outcomes will be analysed using a similar approach. For binary outcomes, logistic regression (binomial distribution with logit link) will be used in place of linear regression. The effect of the intervention will be estimated as the odds ratio and 95% confidence intervals and converted to an absolute risk difference using the Hummel and Wiseman method.^64^ Given that linear mixed models use all data available and make valid inference under the assumption that data are missing at random, the primary analysis will not impute missing data; however, sensitivity analyses will be conducted to assess the robustness of the results under different assumptions about the missing data mechanism. A detailed statistical analysis plan including mock tables will be developed prior to unblinding and database lock.

The economic evaluation of the HP&MBC package is critical to translate this research into practice. It will comprise both a ‘within-trial’ design whereby the individual level costs and outcomes of the two groups (HP&MBC and Standard Care packages) will be included in the evaluation over the duration of the trial. A modelled evaluation will be undertaken to capture full costs and consequences of HP&MBC using the results of this trial and the broader epidemiological literature to estimate likely longer-term health gains, cost impacts, and scale-up costs at the population level. The calculation of quality-adjusted life years will be conducted, thus enabling a cost-utility analysis to be undertaken. Cost-utility analyses are useful to decision-makers as they are associated with inherent value for money connotations. Detailed costing of the HP&MBC approach along with how it has been implemented within each site will be undertaken using information from the researchers, clinical staff, and budgetary personnel.

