### Primary and secondary outcomes

Primary efficacy endpoint:

Changes in social and occupational function from baseline to 12 months, as assessed by the SOFAS.

Key secondary endpoints:

Change from baseline in self-harm, STBs (Brief Non-suicidal Self-injury Assessment Tool, B-NSSI-AT;^54^ Suicidal Ideation Attributes Scale, SIDAS;^55^ C-SSRS, Columbia-Suicide Severity Rating Scale).^56^Change from baseline in depressive symptoms (Quick Inventory of Depressive Symptomatology, QIDS).^57^Change from baseline in quality of life (Recovering Quality of Life Questionnaire, ReQoL).^58 59^Change from baseline in alcohol and substance use (WHO Alcohol, Smoking and Substance Involvement Screening Test, WHO-ASSIST;^60^ AUDIT-C, Alcohol Use Disorders Identification Test – Consumption).^61^Change from baseline in physical health (International Physical Activity Questionnaire – short version, IPAQ^62 63^; height, weight, waist).Change from baseline in metabolic, inflammatory and standard blood measures (metabolic and inflammatory markers, e.g., assessment of triglycerides, cholesterol, glucose, iron).Resource use as well as lifetime and population cost-effectiveness.Costs of the treatment packages based on detailed economic evaluation.

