### Sample size calculation

This trial seeks to recruit 1500 young people, with 750 allocated to active 12-month intervention and 750 to standard clinical care. We anticipate an attrition rate of approximately 10%–20% over short-term follow-up (first 12 months) and up to 30% over the longer-term follow-up (at 24 months). Therefore, we would expect 1350 participants at 6 months follow-up (675 in each arm), 1200 participants at 12 months follow-up (600 in each arm) and 1050 participants at 2 years follow-up (525 in each arm). Assuming that we have at least 434 young people at the 2-year follow-up time point for the primary outcome analysis only, and conservatively assuming a small effect size difference of 0.2 in favour of those young people receiving the active intervention, with α=0.05, we have 95% power. For categorical secondary analyses with a small effect size of 0.2, α=0.05, and power=95%, the sample size at 2-year follow-up is 325 participants. There are also embedded subgroups for secondary analyses (e.g., by baseline suicidal behaviours, depressive subtype, alcohol or other substance misuse, and baseline SOFAS bands). For these subgroups, assuming that we have at least 195 young people at the 2-year follow-up time point for the primary outcome analysis only, and conservatively assuming a medium effect size difference of 0.3 in favour of those young people receiving the active intervention, with α=0.05, we have 95% power. For categorical secondary analyses with a medium effect size of 0.3, α=0.05, and power=95%, the sample size at 2-year follow-up is 144 participants.

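### The primary mixed model uses baseline SOFAS as both response and covariate, so the 12-month standard error is too small and the type I error exceeds 5%

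*Protocol article*

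**What the plan says.** All the elements stand in the Data analysis plan section of the protocol article.

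- **Responses:** a repeated-measures linear mixed model "including all available SOFAS scores measured at months 0, 3, 6, 12, and 24".
- **Fixed effects:** "Fixed effects will include the randomised group, visit as a categorical variable, and the interaction between group and visit".
- **Covariates:** "The baseline SOFAS score will be included as a covariate alongside sex, age, and site (stratification variables". No baseline-by-visit term is listed, so one slope serves all visits.
- **Covariance:** "a random patient intercept will be included". If the model fails to converge, the fallback is a "repeated effect assuming a compound symmetry covariance structure", which has the same marginal form.
- **Contrast:** the model is used to "derive the effect of the intervention at 12 months, expressed as the adjusted mean difference and its 95% confidence interval".

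The Primary and secondary outcomes section words the endpoint as "Changes in social and occupational function from baseline to 12 months, as assessed by the SOFAS". Nothing in the article takes month 0 out of the response or constrains the two arms to a common mean at month 0.

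**The concern.** At month 0 the response equals the covariate, so the slope there is exactly 1. At later visits the slope is lower whenever the correlation is imperfect and the SDs are similar. Fitting one slope pulls it towards 1 and leaves very small residuals at month 0. A random intercept allows one total variance for all visits, so those small residuals lower the variance that the model assigns to month 12.

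The primary interval would then be too narrow and the p-value too small, on the single primary endpoint of a 1,500-person trial planned at α=0.05. The plan applies a similar approach to other timepoints and to secondary outcomes, so the fault can spread.

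**Working it through.** **Inputs from the article.** Model terms are as listed above. There are 750 participants per arm, with 1350, 1200 and 1050 of 1500 expected at 6, 12 and 24 months, that is 90%, 80% and 70% retention (Sample size calculation). The stated target is "with α=0.05, we have 95% power"; α is taken as two-sided because sidedness is not given. The article states no other error rate for this model, so there is no further figure to reproduce.

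**Assumptions.** Retention is 95% at month 3 and dropout is completely at random. SDs and correlations are assumed, since the article gives none.

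**Hand calculation: complete data, equal SDs of 1, common correlation ρ**

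1. Common slope over five visits: b = (1 + 4ρ)/5. For ρ = 0.5, b = 0.60.
2. Residual variance at month 0: (1 − b)² = 0.16.
3. Residual variance at month 12: 1 − 2bρ + b² = 1 − 0.60 + 0.36 = 0.76.
4. Variance the model uses at every visit: (0.16 + 4 × 0.76)/5 = 0.64.
5. Model SE / true SE = √(0.64/0.76) = 0.918.
6. Type I error = 2[1 − Φ(1.96 × 0.918)] = 7.2%.

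The same steps give 6.8% for ρ = 0.3 (ratio 0.931) and 7.55% for ρ = 0.7 (ratio 0.907).

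**With the plan's attrition.** Month 0 is complete while later visits lose participants, so month 0 carries more weight and the fault grows. The table comes from a large-sample calculation: limiting random-intercept estimates, with the model-based SE compared with the true (sandwich) SE. "CS" is compound symmetry, and AR(1) correlation is per visit step.

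| Assumed truth | SE ratio, as written | Type I, as written | Type I, month 0 not a response | Type I, month 12 minus month 0 |
|---|---|---|---|---|
| CS 0.3, equal SDs | 0.916 | 7.3% | 5.0% | 5.4% |
| CS 0.5, equal SDs | 0.901 | 7.75% | 5.0% | 5.45% |
| CS 0.7, equal SDs | 0.889 | 8.2% | 5.0% | 5.5% |
| CS 0.5, follow-up SD 1.25 × baseline | 0.885 | 8.3% | 5.0% | 4.5% |
| AR(1) 0.7, equal SDs | 0.825 | 10.6% | 6.8% | 10.2% |
| CS 0.5, SDs 7/9/10/11.5/11.5 | 0.800 | 11.7% | 7.6% | 6.1% |

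REML simulation with 32,000 null trials per scenario agrees. The model as written gives 7.75% (CS 0.5), 8.2% (CS 0.5, SD ratio 1.25) and 10.5% (AR(1) 0.7). With month 0 removed from the response, the figures are 5.0%, 5.0% and 6.8%.

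**Separating the causes.** In the first four rows, removing month 0 from the response restores 5.0%, so the double use is the whole cause. In the last two rows 6.8% and 7.6% remain. That remainder comes from forcing one variance and one correlation on data that do not have them.

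**The case against.** **The article never calls month 0 a response.** A condensed text might mean that month 0 enters only as the covariate, and a detailed analysis plan is promised before unblinding and database lock. This has some force, but listing month 0 among the repeated scores the model is fitted to most naturally makes it a response. The article also fixes the covariates, covariance and contrast, so an analysis plan written to it would inherit the fault.

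**The contrast could be month 12 minus month 0**, given that the endpoint is worded as a change. Under compound symmetry with equal SDs the error would then be about 5.5%. That stands as arithmetic, but the analysis section names the adjusted mean difference at 12 months, which is the affected contrast. The change contrast is not safe in general either: it gives 10.2% under AR(1) 0.7.

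**The size is not known from the article.** This stands. A reader might infer that the double use alone produces an error of 10% or more. The documents do not support that: such values also need decaying correlations or an SD that keeps rising, and neither is stated. The eligibility limit of SOFAS ≤70 makes a larger follow-up SD plausible but does not give its size.

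**The treatment effect is not biased.** This also stands. A reader might infer a distorted estimate, but under randomisation only the SE, interval and p-value are affected.

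**Conclusion.** The concern holds as a fault in the stated model, not as missing detail. For the contrast the plan names, the model-based SE was too small in every scenario examined.

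Under the plan's own covariance with equal SDs, correlation 0.3 to 0.7 and its stated attrition, the SE is about 8–11% too small and the two-sided type I error is about 7–8% instead of 5%. With decaying correlations or a rising SD it is about 10–12%, of which part belongs to the random-intercept structure. The direction is secure. The size depends on SDs and correlations that the article does not give.

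**What to change.** State that the responses are SOFAS at months 3, 6, 12 and 24 only, with baseline SOFAS as a covariate, and that the primary estimate is the group difference at month 12. A baseline-by-visit term is optional; in these scenarios it does not improve type I error control.

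Also replace the random intercept and its compound-symmetry fallback with an unstructured within-patient covariance, or use robust standard errors. Removing month 0 alone leaves 6.8% and 7.6% in the last two rows of the table. In smaller simulations (1,000–2,000 null trials, month-3 dropout 7%), an unstructured covariance with baseline-by-visit gave 4.6–5.2%.

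Alternatively, keep month 0 as a response with a common baseline mean in both arms, no baseline covariate and an unstructured covariance. The covariance change is essential here: with a random intercept this alternative still gives 8.2% under AR(1) 0.7 and 10.2% with the rising SDs.

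The cost is a few sentences in the protocol and the analysis plan and a few more covariance parameters, which is negligible with 1,500 participants. No extra data are needed, and the change can be made before unblinding.

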## Introduction

There has been increasing recognition of the premature death and persistent disability attributable to the major mental disorders.^1 2^ The largest proportion of this excessive morbidity is attributable to mood disorders, reflecting their early age of onset, high population prevalence, chronicity, and comorbidity.^3^ While significant investments have been made in youth mental health services internationally, there is a lack of substantive evidence for which models of care are optimal for improving illness outcomes.

Mood disorders place young people at risk of prolonged socioeconomic difficulties, even when their mental ill-health subsides.^4 5^ Our work has identified that up to two-thirds of young people in youth mental health services experience poor longer-term functional outcomes.^6 7^ Current evidence suggests that youth mental health services primarily benefit those in the earlier stages of illness and that while brief psychological interventions are effective for reducing psychological distress, they only marginally improve functioning.^8^ Further, current models of care do not appear to be well suited to those with comorbidities, mixed or attenuated symptomatology, or social and occupational complexity. Most treatment plans are focused narrowly on limited treatment choices or ‘steps’ for discrete disorders. They are based on average population effects or clinical experience,^9–17^ and are often inaccurate and inconsistent.

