### Inclusion and exclusion criteria

Participation in this study will be offered to adolescents and young adults aged 15–25 years seeking help for psychological distress and classified as clinical stage 1a, 1b, or 2. The participants must have an initial Social and Occupational Functioning Assessment Scale (SOFAS) score of ≤70,^37^ indicating an impaired social and occupational functioning. Additional exclusion criteria includes acute suicidal or aggressive behaviour requiring alternative care or a depressive syndrome secondary to a primary medical condition. Young people who have a clinically evident intellectual disability (IQ<70 as per medical history review) will be excluded due to the likely difficulty in completing the assessments.

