**Figure 2 F2:**
[figure not shown]
Study flow diagram (consort style).

Individuals referred to the trial will be contacted by a research team member who will provide information about the study and conduct a preliminary assessment of the inclusion and exclusion criteria. Potential participants interested in taking part in the study will then be provided with a copy of the participant information statement (online supplemental material 1), and an appointment will be scheduled for an enrolment visit. During the enrolment/baseline visit (Visit 0), the study will be explained in lay terms and any questions will be answered. Following informed consent, participants will be given relevant assessments to confirm that they meet the inclusion criteria.

10.1136/bmjopen-2023-072082.supp1Supplementary data

Participants who meet the inclusion criteria will be randomised to one of the two treatment arms using a 1:1 individual person randomisation algorithm (using Research Electronic Data Capture (REDCap))^38^ taking age, gender, and treatment centre as stratification factors into account. The care packages will be delivered within the first 12 months of the study by clinicians operating within each service. During this study phase, three study visits will take place: (1) Visit 1 (3 months after trial entry); (2) Visit 2 (6 months after trial entry); and (3) Visit 3 (12 months after trial entry). A follow-up visit (Visit 4) will be conducted 12 months after completion of the care packages (figure 2). All follow-up assessments will be carried out by blinded-independent assessors from the research team.

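### The primary model omits baseline clinical stage, which defines eligibility and is rated for everyone; adding it would give a modest precision gain at no cost (minor)

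*Protocol article*

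**What the plan says.** All references are to the Protocol article.

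- **Eligibility** (Inclusion and exclusion criteria): participants must be "classified as clinical stage 1a, 1b, or 2", with a SOFAS score of 70 or below.
- **Measurement** (Assessments, Table 2): stage is researcher-rated at months 0, 3, 6, 12 and 24. The baseline rating is used to check eligibility, and randomisation follows that check (Study course and procedures).
- **Rationale** (Introduction): the protocol reports evidence that "youth mental health services primarily benefit those in the earlier stages of illness".
- **Randomisation** (Study course and procedures): the algorithm works by "taking age, gender, and treatment centre as stratification factors into account".
- **Primary model** (Data analysis plan): besides group, visit and their interaction, "The baseline SOFAS score will be included as a covariate alongside sex, age, and site (stratification variables"). This list is not marked as a set of examples.
- **Subgroups** (Sample size calculation): the list reads "e.g., by baseline suicidal behaviours, depressive subtype, alcohol or other substance misuse, and baseline SOFAS bands". It is marked as a set of examples.
- **Later plan** (Data analysis plan): a detailed statistical analysis plan is to be written before unblinding and database lock.

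**The concern.** Stage is the variable by which the trial defines its population, and the protocol's own background treats it as relevant to outcome under existing care. The standard care arm builds on the usual service systems, so stage may well predict 12-month functioning. Because stage is an entry criterion, its baseline value should be known for every randomised participant. Leaving it out of a covariate list that is otherwise spelled out passes over a complete, pre-randomisation and plausibly prognostic variable.

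What is at stake is limited: some precision in the primary contrast, and a stated place for stage when readers ask whether the effect differs between non-specific, attenuated and full-threshold presentations.

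**Working it through.** **1. Where stage appears.** It is in the eligibility criteria and in Table 2 at every visit. It is not in the strata, the primary model's covariates or the example subgroups.

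**2. The plan's own power figure.** The Sample size calculation gives 434 participants for an effect of 0.2 at 95% power. A two-arm comparison of means at two-sided 0.05 needs 650 per arm; 434 gives 55% power if it is a total and 84% if it is per arm. The figure therefore does not reproduce as a two-arm contrast. That is a separate matter and does not involve stage. The benchmark below uses the 600 per arm that the protocol expects at 12 months, the primary time point.

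**3. Precision gained from stage as a covariate.** Inputs are n = 600 per arm and d = 0.2 (Sample size calculation), and two-sided alpha 0.05 (the sidedness is assumed). Let R² be the share of the remaining outcome variance that stage explains beyond the covariates already in the model. The document gives no value, so 2%, 5% and 10% are assumed.

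SE = √(2/600) × √(1 − R²), with √(2/600) = 0.0577

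Power = Φ(0.2/SE − 1.96)

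| R² | 0.2/SE | Power |
|---|---|---|
| 0 | 3.464 | 93.4% |
| 2% | 3.499 | 93.8% |
| 5% | 3.554 | 94.5% |
| 10% | 3.651 | 95.5% |

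In sample-size terms the gain is 600/(1 − R²), which is about 612, 632 or 667 per arm. The benchmark treats the 12-month contrast as a simple comparison of two means and ignores the earlier visits.

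**4. What a group-by-stage term could show.** The stage mix and the effects by stage are not stated. For illustration, collapse stage into two groups: a share f with effect 0.2 and the rest with none.

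SE of the interaction = √(2/(600f) + 2/(600(1 − f)))

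Power = Φ(0.2/SE − 1.96)

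| f | SE | Interaction power |
|---|---|---|
| 1/3 | 0.122 | 37% |
| 1/2 | 0.115 | 41% |
| 2/3 | 0.122 | 37% |
| 0.8 | 0.144 | 28% |

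The term would usually miss a difference of this size, so it can only be supportive.

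**5. Chance imbalance.** With 750 per arm and no stratification by stage, the 95% range of imbalance for a stage with prevalence 20% to 50% is 1.96 × √(2p(1 − p)/750), about 4 to 5 percentage points either way. That is small and gives no reason to change the strata.

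**The case against.** The strongest reply is that nothing here is wrong. The subgroup list is explicitly one of examples, the detailed analysis plan is not shown, and subgroup definitions are commonly left to it. The protocol also handles severity in another way. The Introduction calls functioning at presentation a key factor, entry requires impaired SOFAS at every stage, baseline SOFAS is in the model, and SOFAS bands are an example subgroup. In addition, the Introduction's sentence on stage concerns existing services, not HP&MBC against standard care, and it goes on to say that brief psychological interventions improve functioning only marginally.

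Most of this stands. The absence of stage from the example subgroups is no defect in itself, and baseline SOFAS may already carry much of what stage would add. The reply does not reach the covariate list, which the article sets out without marking it as illustrative.

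A reader might infer more: that early-stage participants do well anyway, that they dilute the overall effect, and that a small result could then not be interpreted. The documents do not support this. Under randomisation the overall difference is a valid average for the enrolled mix whether or not stage is modelled. No effect by stage is stated. If 20% of participants had no benefit, the average effect would be 0.16 and power 79%, but that loss comes from the assumed effect modification and would be the same with stage in the model. Nor would a later analysis by stage necessarily be post hoc, since the detailed plan is still to be completed before unblinding.

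**Conclusion.** The point holds as a minor one. The primary model leaves out a baseline variable that defines the population and should be complete. The overall 12-month estimate is not biased by this and remains interpretable. The cost is a modest loss of precision: about 0.4 to 2.1 percentage points of power at 600 per arm and a difference of 0.2, if stage explains a further 2% to 10% of variance. That range is assumed, and the gain could be nearer zero if baseline SOFAS already captures most of what stage predicts. A stage-by-treatment analysis is worth naming in advance for its credibility. With roughly 28% to 41% power under the assumed mixes, a non-significant interaction would not show that the effect is the same across stages.

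**What to change.** - **Data analysis plan:** add baseline clinical stage (1a, 1b, 2) as a fixed covariate in the primary model.
- **Sample size calculation, subgroup list, or the forthcoming analysis plan:** as a secondary and supportive step, name clinical stage beside the existing examples. Specify a group-by-stage term for the 12-month SOFAS contrast; in the repeated-measures model this means letting the group-by-visit effect differ by stage. Report the adjusted difference with its 95% CI in each stage, and state that interaction power is low.

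Strata, sample size and data collection stay as they are. The cost is a change of wording before unblinding, two degrees of freedom in the primary model, and one further secondary analysis whose within-stage estimates will be imprecise.
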